## Abstract

**Introduction:**

Chronic musculoskeletal pain is a highly prevalent, complex and distressing condition that may negatively affect all domains of life. In view of an active inference framework, and resting on the concept of allostasis, human movement per se becomes a prerequisite for health and well-being while chronic pain becomes a sign of a system unable to attenuate an allostatic load. Previous studies on different subgroups of chronic pain conditions have demonstrated alterations in gait kinematics and muscle activity, indicating shared disturbances in the motor system from long-term allostatic load. We hypothesise that such alterations exist in heterogenous populations with chronic musculoskeletal pain, and that exposure to acute and controlled exercise may attenuate these alterations. Therefore, the main aim of this study is to investigate the acute effects of exercise on gait kinematics and activity of the back and neck muscles during diverse walking conditions in patients with chronic musculoskeletal pain compared with a reference sample consisting of healthy participants.

**Methods and analysis:**

This two-sample two-armed parallel randomised controlled laboratory trial will include 40 participants with chronic musculoskeletal pain (>3 months) and 40 healthy participants. Participants will be randomly allocated to either 30 min of aerobic exercise or rest. Primary outcomes are gait kinematics (walking speed, step frequency, stride length, lumbar rotation, gait stability) and muscular activity (spatial and temporal) of the back and neck during diverse walking conditions. Secondary outcomes are variability of gait kinematics and muscle activity and subjective pain ratings assessed regularly during the trial.

**Ethics and dissemination:**

The study has been approved by the Regional Ethics Review Board in Uppsala, Sweden (#2018/307). Findings will be disseminated via conference presentations, publications in peer-reviewed journals and engagement with patient support groups and clinicians.

**Trial registration number:**

NCT03882333.

Strengths and limitations of this studyTo our knowledge, this will be the first randomised controlled laboratory trial investigating the acute effects of aerobic exercise, as active inference, on gait kinematics and muscular activity in a heterogenous group of patients with chronic musculoskeletal pain.As long-term aerobic exercise is ultimately the result of regular sessions of aerobic exercise, studying effects induced by a single session of aerobic exercise will provide important insights into exercise and its role in the rehabilitation of chronic pain conditions.The study will incorporate objective measures of gait kinematics and muscle activity from continuous overground walking by using modern wireless sensors, thus replicating real-world conditions of functional movement.While complete blinding is not possible post intervention, due to the nature of exercise, care will be taken to minimise investigator bias by using automated recording protocols.

## Introduction

Chronic musculoskeletal pain is a highly prevalent and complex condition that continues to challenge clinicians and academics and as such constitutes a major health and well-being burden.^1 2^ The International Association for the Study of Pain defines chronic pain as ‘pain which has persisted beyond normal tissue healing time’, which, in the absence of other factors, is a pain condition lasting for more than 3 months.^3^ A condition with chronic musculoskeletal pain may be referred to as chronic primary pain^4^ and should be seen as a disease in its own right.^5^ Chronic musculoskeletal pain can negatively affect physical movement and functioning, sleep, social interaction, quality of life and work ability,^6^ in essence all domains of life.

In the light of an active inference framework,^7–9^ based on the free energy principle proposed by Friston^10 11^ and resting on the concept of allostasis,^12^ any living system becomes a model of the world it inhabits. Then, through the process of active inference, it attempts to maximise the proof of its own existence (chances of survival) by minimising prediction errors (variational free energy) through perception and action. The physiological concept of allostasis can be described as achieving stability through change,^12^ in which the rate of change influences the process of adaption. In addition, living things may be defined by their ability to move autonomously, be it of bodies, limbs or cells, making movement a key driver of allostasis through sensory palpation of the world. In view of this, human movement, from cell respiration to locomotion, may constitute the major source of active inference on which the organism builds and maintains its model, making human movement of all sorts pertinent to long-term health and prosperity by facilitating the changes that are needed for stability.

Building on this notion, in a healthy context acute pain can be viewed as a precision signal for learning and control, with the main function being motivational to direct both short-term and long-term motor behaviour away from harm.^13^ Chronic musculoskeletal pain, on the other hand, is suggestive of a living system in distress and may be explained by the creation and maintenance of abnormal priors that are afforded abnormal attention in a self-evidencing system.^7 14^

This reasoning is—we believe—in line with earlier theories such as the body-self neuromatrix model,^15^ the theory of moving differently in pain^16^ and effectively aligning with concepts such as sensitisation,^17 18^ and ultimately depression^19^ within chronic pain populations, as well as recent theory on active interoceptive inference.^20^ Then chronic pain can also be viewed as the consequence of an allostatic overload from unresolved prediction errors of the system’s lower level predictions about its internal and external milieu.^17 19 21–24^ These prediction errors in lower level predictions may manifest themselves at higher levels as fear avoidance behaviour of movement^25^ and intolerance of uncertainty,^26^ which lead to the further reduction of physical activity.^27–29^ This relative sensory deprivation^30 31^ that is induced by sedentary behaviour may disable self-organisation normally driven through allostasis, leading to aberrant neurosignatures (models) of painful states. In essence, chronic musculoskeletal pain becomes a pathophysiology with a self-fulfilling hypothesis of pain as the systems only solution to minimise prediction errors. Building on this notion, physical activity and exercise, or simply human movement, can be viewed as active inference and as such may facilitate a return to allostasis and less painful future states by promoting the flexible reassignment of precision weighting that alters the individual’s prediction about their body and their world.^32^ This implies that adding physical activity or exercise to a rehabilitation programme may simply be reintroducing something essential that was engineered away generations ago.

From this active inference view of chronic pain, it is understandable that a biopsychosocial approach has gained traction in the treatment of chronic pain conditions,^6 33–35^ since such interdisciplinary treatment delivered by a team of allied health professionals involves a combination of physical activity and exercise, psychological interventions, pharmaceutical treatments and patient education all acting as active inference^33^ enabling a return to less painful states.

Given the fact that the musculoskeletal system is crucial to human locomotion or functional movement, a large body of research has focused on the effects of chronic pain on functional movement. There is now moderate-to-strong evidence that individuals with persistent low back pain demonstrate differences in gait kinematics,^34^ that individuals with non-specific low back pain demonstrate impaired postural control when standing^35^ and that individuals diagnosed with fibromyalgia demonstrate an altered gait compared with healthy individuals.^36^ Neuroimaging studies have reported functional brain changes related to sensorimotor impairment in individuals with low back pain,^37^ irritable bowel syndrome,^14^ fibromyalgia^38^ and migraine,^39^ suggestive of shared disturbances of the motor system across different diagnoses. The overall finding is that persons with chronic pain conditions walk slower, with a lower step frequency, shorter step length and with a greater amplitude of back muscle activity.^34–36^

However, based on the notion of a shared disturbance, it is currently not known if the altered gait patterns identified in specific subgroups of chronic pain patients may generalise to wider populations of chronic musculoskeletal pain patients and if they could be used as markers of functional movement impairment in these populations. There is a paucity in how exercise, viewed as active inference, can have an acute effect on the motor control of walking in humans, especially in adaptions to perturbations such as faster walking speeds or dual tasks and if this is related to long-term sedentary behaviour.

Therefore, the main aim of this study is to investigate the acute effects of exercise as active inference on gait kinematics and activity of the back and neck muscles during diverse walking conditions in patients with chronic musculoskeletal pain compared with a reference sample consisting of participants without chronic musculoskeletal pain.

Our hypothesis is that a wide sample with chronic musculoskeletal pain will walk at lower speeds with lower step frequency and stride lengths but with increased muscle activity in the back and neck and that these differences will increase with task difficulty and begin to attenuate acutely by exercise.

## Materials and methods

### Trial design

The study consists of a two-sample two-armed parallel randomised controlled laboratory trial (RCT) that will be conducted at Dalarna University, Sweden (figure 1). The main sample consists of patients with chronic pain who will be randomised into one of two arms: an intervention group performing a single session of acute aerobic exercise (30 min stationary cycling) or a resting control group. The reference sample consists of participants without chronic musculoskeletal pain who will follow a similar RCT procedure, with the purpose being to investigate whether the acute response to exercise is unique for patients with chronic pain as our hypothesis proposes, or if it is just a general effect that would be seen in any population. The trial will comply with Consolidated Standards of Reporting Trials and Standard Protocol Items: Recommendations for Interventional Trials guidelines with Patient Reported Outcomes (SPIRIT).^40–42^ A completed SPIRIT checklist for the trial can be found in online supplemental appendix 1. Data will be collected between January 2019 and May 2021.

10.1136/bmjopen-2022-069747.supp1Supplementary data

**Figure 1 F1:**
[figure not shown]
Participant flowchart. MPI, Multidimensional Pain Inventory; PCS, Pain Catastrophizing Scale.

For our primary outcome, a total estimated sample size of n=80 (n=20 in each of the four randomised groups) was determined based on previous studies using similar design and wearable technology.^43 44^ A supplementary power calculation was conducted using normalised right-side erector spinae longissimus back muscle activity collected from the initial 20 participants to confirm the adequacy of the sample size. The analysis confirmed that a total sample size of n=80 is required to achieve a statistical power of 80% at a significance level of α=0.05 (two tailed) to detect a 25% difference between patients and participants without musculoskeletal pain.

### Participants and setting

This trial includes 80 participants. Patients (n=40) that visit primary and specialist pain clinics in Region Dalarna for evaluation or treatment of chronic musculoskeletal pain (> 3 months), as well as an age-matched and gender-matched convenience sample of participants without musculoskeletal pain (n=40), will be simultaneously recruited. The physiotherapists treating or evaluating potential participants at the cooperating clinics will act as liaisons to inform patients of the study and those interested in participation will be asked to provide their contact information. Researchers will then contact all potential participants by telephone and email prior to the laboratory visit, to perform a preliminary screening of eligibility criteria before scheduling a laboratory visit.

#### Eligibility criteria

Participants aged 18–67 years will be included. Patients will be in assessment and/or treatment of chronic (>3 months) musculoskeletal (neck and/or low back) pain or widespread pain in primary or specialist pain care in Region Dalarna. Exclusion criteria: (1) any coexisting medical condition that would restrict safely participating in the exercise intervention, (2) previous spinal surgery, (3) inability to perform unsupported indoor walking, (4) inadequate Swedish or cognitive ability to provide consent and understand information and instructions, (5) pregnant in second or third trimester or childbirth in the last 3 months, (6) allergies to adhesive tape used for sensor application, (7) major hearing impairment effecting performance of auditory 1-back test, (7) pain caused by malignancies or systemic diseases, or localised pain in lower extremities only.

#### Randomisation, allocation concealment and blinding

Participants will be randomly assigned to either the intervention or control group at a 1:1 allocation ratio, using stratified block randomisation with a fixed block size of six within the chronic musculoskeletal pain and no chronic pain strata. Allocation information is kept in opaque sealed envelopes and will not be disclosed to participants or researchers until all baseline walk trials are completed. All data collection will be automated in preprogrammed sequences and participant instructions read verbatim to minimise any investigator bias influencing participants’ behaviour. Participants will not be informed of the hypotheses of the study, and the researcher performing the data analyses will be blinded to group allocation.

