### Trial procedure, instruments and data collection

The entire trial procedure at the laboratory is expected to take approximately 3 hours and will be supervised by two researchers. On arrival at the laboratory, eligibility screening, presentation of the study procedures and collection of informed consent (online supplemental appendix 2) will be performed. Participants will complete the following questionnaires before commencing any testing: (1) participant characteristics (age, sex, educational level, occupational status, pain locations, pain duration) including two validated items with questions about physical activity.^48^ Participants with chronic musculoskeletal pain will also complete the following two questionnaires relating to pain experiences: (2) the Pain Catastrophizing Scale,^49^ which contains 13 items regarding participants’ thoughts and feelings associated with pain, with a total score ranging from 0 to 52, with higher scores representing higher pain catastrophising and (3) the West Haven-Yale Multidimensional Pain Inventory, which is a questionnaire that measures the psychosocial, cognitive and behavioural effects of chronic pain.^50–53^

10.1136/bmjopen-2022-069747.supp2Supplementary data

A researcher will then record participant body height using a stadiometer (Harpenden Stadiometer, Holtain Limited, Crosswell, UK) and body weight using a weighing scale (Midrics, Sartorius AG, Goettingen, Germany). Participants will be introduced to the 1-back test^54^ and listen to a 30 s practice sequence, then two 30 s 1-back baseline tests will be recorded with participants in a seated position. The 1-back test will be performed with a pair of minimally intrusive wireless handsfree on-ear headphones connected via Bluetooth to a PC using Audacity Software V.2.3.0. Participants will listen to an audio file consisting of a randomised number sequence and will be instructed to respond as quickly and accurately as possible to audio prompts, repeating the digit before the last one in the consecutive sequence during the entire 1-back walking trial. All responses will be recorded.

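### One fixed block size of six lets staff who know it and keep a tally foresee about 23% of allocations before the baseline walks, which sealed envelopes cannot prevent.

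*Protocol article*

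**What the plan says.** The section Randomisation, allocation concealment and blinding sets the ratio: "Participants will be randomly assigned to either the intervention or control group at a 1:1 allocation ratio". It sets the method as "using stratified block randomisation with a fixed block size of six within the chronic musculoskeletal pain and no chronic pain strata". On concealment it says: "Allocation information is kept in opaque sealed envelopes and will not be disclosed to participants or researchers until all baseline walk trials are completed". The same section lists other safeguards: preprogrammed data collection, scripted instructions, participants who are not told the hypotheses, and an analyst blinded to group.

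The sample-size paragraph under Trial design gives "a total estimated sample size of n=80 (n=20 in each of the four randomised groups"). Participants and setting gives 40 in each stratum: "Patients (n=40) that visit primary and specialist pain clinics in Region Dalarna" and "participants without musculoskeletal pain (n=40), will be simultaneously recruited". It also says that researchers contact, pre-screen and book every potential participant. Under Trial procedure, instruments and data collection, eligibility screening and consent take place on arrival, and the visit "will be supervised by two researchers". The strengths and limitations box accepts that blinding cannot be complete once the intervention has been given.

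**The concern.** A sealed envelope hides its own contents. It does not hide what the envelopes already opened imply about the next one. With a single block size, anyone who knows that size and remembers the allocations so far in a stratum can tell when one arm of the current block is used up, and the rest of the block is then known. Here each arm becomes known to researchers during the visit, so a tally is easy to keep.

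Three decisions made before the envelope is opened could be affected: whether a borderline candidate is judged fit to take part (the first exclusion criterion concerns safety in the exercise session), who is booked next, and how the baseline walks are conducted. The reference sample is a matched convenience sample, which leaves some latitude over whom to invite. The baseline walks are the starting point for every primary outcome. Foreknowledge at these steps is the route to selection bias that concealment is meant to close.

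**Working it through.** **Inputs from the article:** block size 6, ratio 1:1 (so 3:3 per block), two strata, 40 places per stratum, 20 planned per group.

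**The plan's own figure.** 4 × 20 = 2 × 40 = 80, so the counts agree. The power calculation behind 80 compares patients with reference participants, 40 v 40. No SD is given, so it can only be back-solved: (1.960 + 0.842) × √(2/40) = 0.626 SD, and 0.25/0.626 implies an SD of about 0.40 of the mean. Nothing below depends on it.

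**Places known with certainty in a complete block.** There are C(6,3) = 20 equally likely sequences.
- Places 1 to 3: never determined.
- Place 4: determined if the first three are all one arm, 2/20 = 0.10.
- Place 5: determined if the first four split 3:1, 2 × C(3,3) × C(3,1)/C(6,4) = 6/15 = 0.40.
- Place 6: always determined, 1.00.
- Sum: 1.5 of 6 = 25%.

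**Over the planned stratum.** 40 = 6 × 6 + 4: six complete blocks and the first four places of a seventh. Expected determined places: 6 × 1.5 + 0.10 = 9.1 of 40 = 22.75%, or 18.2 of 80. A simulation of 50,000 lists gave 22.8%.

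**Best-guess rate.** Guessing the arm with more places left in the block is right with probability 0.5, 0.6, 0.6, 0.7, 0.7 and 1.0 at places 1 to 6. That is 4.1 of 6 in a complete block, and 0.5 + 0.6 + 0.6 + 0.7 = 2.4 in the unfinished one. Over 40 places: (6 × 4.1 + 2.4)/40 = 67.5%, against 50% by chance.

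**Alternatives.**
- A known fixed block that divides 40 does not solve the problem. The certain share is 33.3% for blocks of 4, 20.0% for 8 and 16.7% for 10.
- Randomly ordered 4s and 8s that sum to 40, with the order undisclosed: an observer who knows the two sizes but not their order is certain at about 10% of places. This assumes that 4 and 8 are equally likely and was found by simulation. The best-guess rate is about 68%, no better than now.
- If the order leaks, the gain is lost. For example, four 4s and three 8s give 4 × 1.333 + 3 × 1.6 = 10.13 of 40 = 25.3% certain.

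**Side point, group sizes.** The first four places of the seventh block split 2:2 with probability C(3,2) × C(3,2)/C(6,4) = 9/15 = 0.60. A 21:19 split therefore has probability 0.40 per sample. Its variance cost is (1/21 + 1/19)/(2/20) = 1.0025, which lowers a within-sample power of 80% to 79.9%.

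**The case against.** The strongest reply is that the harm is conditional. The article does not say that visit staff know the block size, who made the list, or that those who book participants are the two who supervise the visit. A condensed article may leave such details to the full protocol. This stands: a reader might infer that researchers will in fact know the coming arm, and the text does not support that. It supports only that the stated scheme permits the deduction and that no withholding of the size is mentioned.

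The safeguards also count. Automated recording, scripted instructions and a blinded analyst limit the effect on measurement and analysis. Participants do not know their arm at baseline, and two of the three walking conditions are at habitual speed. But none of this protects screening or scheduling.

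A reader might also take the 68% guess rate as harm that varied blocks would remove. They would not: the rate is about the same before and after, and only the share known with certainty falls.

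Finally, a reader might infer that "n=20 in each of the four randomised groups" is contradicted because six does not divide 40. The article presents the total as an estimate, the departure is at most one participant each way, and the 40 v 40 power calculation is untouched. That is not an error in the sample size.

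**Conclusion.** The concern holds as a design weakness in how the sequence is built. A single block size of six, in a trial where researchers learn each arm at the visit, makes 22.75% of places per sample (25% in complete blocks) certain in advance. For those places the envelopes alone do not secure the article's aim of concealment until the baseline walks are done. The figure rests on two assumptions: that the staff concerned know or infer the size, and that they follow earlier allocations within the stratum. How much bias would follow cannot be calculated from the article. The existing safeguards confine the exposure mainly to screening, booking and the conduct of the baseline walks. Once the envelope is opened the arm is known anyway, so predictability adds nothing there.

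**What to change.** For places not yet allocated, replace the fixed block of six with randomly ordered block sizes that sum to 40 in each sample, for example 4s and 8s, and keep the sizes and their order from those who screen, book and test. This lowers the certain share from 22.75% to about 10% even if the two sizes become known, and gives exactly 20:20. If part of the list has been used, finish the current block and let the new sizes sum to what remains. After three blocks of six, for instance, 40 − 18 = 22 places remain, which 8 + 8 + 6 in random order would fill. The cost is a new list and new envelopes.

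Trial design gives data collection as January 2019 to May 2021, and the article's supplementary files carry a 2022 identifier, so allocation may already be complete. In that case the sequence cannot be changed. Report who knew the block size, and compare baseline values at determined and undetermined places. This needs only the allocation list and data already collected.
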